## **Procedures for notification of severe and unexpected adverse events.**

The sponsor will notify the AEMPS of all suspected severe and unexpected adverse events associated with the study drugs in accordance with current legislation.

The maximum period for notification will be 15 days, except when the suspected severe and unexpected adverse event has lead to the death of the subject, or has placed the subject’s life in danger. In this case, the event will be reported within the 7 natural days after knowledge of the event. The information can be completed within the following 8 days.

Reports to the AEMPS will be by [contact] or mail to Area de ensayos clínicos de la Subdirección General de Medicamentos de Uso Humano, [name].

Reports to the CAM will be via the contact person in Dirección General de Farmacia y Productos Sanitarios de la Consejería de Sanidad y Consumo de la CAM, Area de Investigación clínica y EPAs, [name]. [contact] [contact] E-mail: [[contact]](mailto:[contact]).

Reports to the IRB of Hospital Ramón y Cajal: [contact], at [[contact]](mailto:[contact]), or directly to [name] IRB Secretary.

# ETHICS

## **General and specific norms for investigators**

The investigators will adhere strictly to the stipulations of this protocol, and will complete all the case report forms, which they will duly send to the sponsor or collaborating entity chosen by the sponsor to analyze the data.

The trial will be carried out in accordance with the recommendations for clinical trials and drug evaluation in humans, which appear in the Declaration of Helsinki (Appendix A), reviewed in Tokyo, Venice, Hong-Kong, South Africa, and Edinburgh (2000) and in current Spanish legislation on clinical trials.

## **Informed consent**

Before the study starts, all the participating subjects will be informed and will give their written informed consent. The informed consent form appears in Appendix D. The participant will receive a copy of this information sheet to take away.

## **Security and confidentiality**

The information published and obtained as a result of this study is considered confidential and must be treated as such at all times. The study subjects will be identified only by their study subject code. Both the investigators responsible for the clinical trial and a representative of the sponsor or the Health Authorities will have access to the information recorded during the study. If the results of the study are published, the identity of the volunteers will not be revealed.

## **Content of the trial budget**

Investigator remuneration for this trial etc. is specified in the financial report, Appendix B of the protocol.

## **Insurance**

The Fundación para la Investigación Biomédica of the Hospital Ramón y Cajal has a civil liability insurance policy fulfilling the requirements of Royal Decree 223/2004 that will provide compensation and indemnity to the participants in the case of damage to their health or any injuries they might suffer.

Furthermore, this policy covers the responsibilities of the sponsor, investigator team, and the Hospital Ramón y Cajal (Annex IV).

# PRACTICAL CONSIDERATIONS

## **Responsibilities of the trial participants**

The investigators will adhere to the norms of Good Clinical Practice and will know and follow the standardized operating procedures of the Infectious Diseases Service.

All the information recorded during the trial will be noted directly on the case report form (see Annex 1). When a correction is made, the person making the correction should write his/her initials and the date.

Auxiliary staff will follow the instructions given by the investigator concerning blood sample extractions, management thereof, and other complementary examinations.

Before the study, patients must receive oral and written information concerning the design and objectives of the study and the possible risks involved with it (Appendix D). If they then agree to participate, they must sign the consent form. This will not prevent them from later revoking this decision and leaving the study at any time and for any reason.

Patients will receive instructions on the need to strictly adhere to the instructions given by the investigators. They will be informed of the need to contact the investigators if any incidence arises during the study. The means to do this must be provided during the outpatient period of the study.

## **Deviations from the protocol**

The investigators present in these circumstances will make a complete report of the deviation and the reason for it in the CRF. If the deviation involves the inclusion/exclusion criteria, the investigators will contact the monitor by telephone to report on the deviation.

## **Filing of the documentation**

There is a document file for all the data. These will be on paper and computerized for 15 years after the study ends. This file must contain the following:

1. Ethics committee approval of the protocol and the informed consent form.
2. Copy of the approved written informed consent form and protocol with any applicable amendments.
3. Any study correspondence with the sponsor during the study.
4. Any correspondence with the ethics committee.
5. List of members of the ethics committee that approved the study protocol.
6. Signed acceptance of the protocol.
7. *Curriculum vitae* of the Chief Investigator and of the other investigators who make up the investigator team.
8. Register of the signatures of the members of the investigator team.
9. Reports of severe AE.
10. Contract between the sponsor and the investigator team.
11. List of the participant identities.
12. Copies of the CRF.

## **Identification of the samples**

The study medication will be provided by Laboratorios Pfizer, S.L., manufacturers of the product, and will be labeled according to the recommendations of Royal Decree 223/2004.

## **Amendments to the protocol**

Neither the investigator nor the monitor nor the sponsor will modify this protocol without the previous permission of the other parties. The modification should be recorded in writing. Any change in the research activity, except those necessary to eliminate an immediate apparent risk for the patient must be reviewed and approved by the ethics committee before their implementation. The sponsor must send the amendments to the protocol to the health authorities, and the modifications may need to be reviewed and approved by the ethics committee.

## **Acceptance by the investigator**

The investigator commitment is included in Appendix C.

## **Conditions for publication**

The results of the present study will be published, and the permission of the investigators and the sponsor will be required. A copy of the manuscript to be published must be made available to the monitor and the sponsor 15 days before it is sent to the editor. Similarly, the confidentiality of patient identity will always be respected.

# STATISTICAL ANALYSIS

This is an exploratory pilot study that is trying to prove a concept. Therefore, it is not possible to estimate the size of the sample necessary to demonstrate this. A treatment group of 10 patients has been considered necessary, based on data from previous studies on the same subject, which have used between 4 (Lehrman et al. Lancet 2005) and 11 (Chun et al. J Clin Invest. 2005) patients.

The longitudinal and cross-sectional analysis of the frequency data of infected cells will be carried out using random-effects regression models. In these models, the variable time will be introduced as an independent variable assuming linear kinetics. The frequencies of infected cells will be calculated using a parametric maximum likelihood method described elsewhere for limiting dilution experiments (Myers, L.E., McQuay, L.J. & Hollinger, F.B. Dilution assay statistics. J. Clin. Microb 1994; .32, 732–739) and will be expressed as infectious units per million (IUPM) of resting CD4 T cells. The gradient of the log10 reduction in IUPM will be estimated according to time from the start of therapy. This modelling process will be carried out in 2 approaches. In the first, 2 models will be made to estimate the gradients of log10 reduction in IUPM in the group of patients treated with the drug (n=10). Assuming linear reduction kinetics over time, the half-life will be calculated. The second approach will estimate a single model of the same characteristics as the previous ones but will include an interaction term between time and the treatment received. Given the design of the pilot study (concept), the statistical results will be reported as the estimations together with their standard errors without placing emphasis on the P values found. All the analyses will be carried out using STATA ver 9.0.

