# Rationale

The presence of a pool of cells latently infected by HIV-1 in patients taking HAART and with a viral load below 50 copies/mL is the main limitation to eradication of the virus from the body. This viral reservoir prevents antiretroviral therapy from being interrupted; therefore, patients are obliged to continue with treatment for a period calculated to be greater than 60 years.

Despite the important advances in knowledge of the biology of this reservoir, we still have no real knowledge about its dynamics. The opportunity to carry out a clinical trial for the first time with CCR5 coreceptor antagonists is exceptional, since the results could provide important information on the nature of this reservoir.

If maintenance of the reservoir is a dynamic process, inclusion of CCR5 inhibitors is expected to lead to a reduction in the size of this reservoir. This effect could be critical when including IAT (viral reactivation), since, in theory, it would be necessary to act on a smaller reservoir. Current consensus is that it would be necessary to act on almost 100% of the viral reservoir (approximately 106 cells).

The study has also been designed to enable us to understand the biochemical and molecular mechanisms by which certain drugs can induce viral reactivation in vitro as a previous step to a clinical trial aimed at reactivating viral latency and eradicating HIV-1 from the body.

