## **Study development**

Patients who fulfill the inclusion criteria will undergo the following procedures:

- Clinical history including duration of antiretroviral therapy and demonstrated period of undetectable viral load.
- Complete physical examination including height, weight, and temperature.
- Heart rate and systolic and diastolic blood pressure.
- Blood count, biochemistry, and urinalysis as described in section 8.3.2 of this protocol. Women will undergo a pregnancy test.
- Determination of viral load using ultrasensitive methods and CD4+ T lymphocyte count in blood samples.
- Determination of viral tropism.
- Measurement of the size of the reservoir of latent virus and its reactivation capacity.

Blood samples will be extracted by conventional phlebotomy on the dates set out in the study time line. The determinations will be carried out in the study center, with the exception of the determination of viral tropism and measurement of the size of the latent reservoir. For the former, samples will be sent to the Monogram® laboratories in the United States of America, as this is the only laboratory in the world approved for phenotyping coreceptors. For the latter, the samples will be taken in two laboratories: Infectious Diseases Laboratory from Hospital Ramón y Cajal and to the Molecular Immunobiology Laboratory of the Hospital General Universitario Gregorio Marañón (Dra. [name]) in Madrid.

After inclusion each patient receives, in addition to their usual medication, a CCR5 coreceptor antagonist entry inhibitor (maraviroc) in a dose of 150-600 mg every 12 hours according to technical data and previous treatment.

Treatment will be administered for at least 12 months. During this period, viral load will be measured using ultrasensitive methods, the CD4 count will be determined in peripheral blood, and the size of the reservoir of latent virus will be measured every 3 months after a blood extraction of 350 of total blood. After the intensification period with maraviroc and after drug suspension, patients will be following up during two additional visits according the study plan.

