**STUDY METHODS**

**LATENTLY HIV-1-INFECTED MEMORY T CELLS QUANTIFICATION**

Two baseline determinations (three months apart) will be performed to investigate the accuracy of the method and the stability of the reservoir. We carried out a previously described co-culture assay. Briefly, PBMC will be isolate from 300 ml of heparinized whole blood using Ficoll density gradient centrifugation (Lymphocytes Isolation Solution, Rafer, S.L Zaragoza, Spain). Resting CD4+ T cells (CD4+/HLA-DR-/CD25-) will be isolate and purified using magnetic beads according to the manufacturer’s recommendations (Miltenyi Biotec, S.L. Bergisch Gladbach, Germany). CD4+ T-cell purity greater than 99% with less than 0.4% activation will be confirmed by flow cytometry. The isolated resting CD4+ T cells will be plate in replicate limiting dilutions and co-culture with allogenic irradiated PBMC from seronegative donorsand phytohemaglutinin (PHA). The co-culture will be incubating with 5% of CO2 and 37ºC.

The activated cell culture will be fed once a week with PBMC from healthy donors after depletion of CD8+ T cells. On days 15 and 21, culture supernatants will tested for HIV-1 replication using the HIV-1 p24 antigen assay (Innogenetics Diagnostica Iberia, S.L Tarragona, Barcelona, Spain). Infected cell frequencies will be determine by the maximum likelihood method and expressed as infectious units per million (IUPM) resting CD4+ T cells. The accuracy of the measurement will depend on the number of replicates tested at each cell dilution.

RESIDUAL VIREMIA QUANTIFICATION

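### Both planned models force a straight line in time and convert its slope to a half-life, so an early fall that then levels off would be reported as continuing decay

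*Protocol*

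**What the plan says.** Section 11 of the protocol fixes the form of the time effect: "In these models, the variable time will be introduced as an independent variable assuming linear kinetics". The estimand is one slope: "The gradient of the log10 reduction in IUPM will be estimated according to time from the start of therapy". It is then converted: "Assuming linear reduction kinetics over time, the half-life will be calculated". The second approach has the same characteristics as the first and "will include an interaction term between time and the treatment received", so it too is linear in time. Section 11 names no categorical-visit, piecewise or curved time effect.

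The Rationale makes the expected effect conditional on the reservoir being dynamically maintained. In that case "inclusion of CCR5 inhibitors is expected to lead to a reduction in the size of this reservoir". The subsection on in vivo viral latency sets out two opposing views on whether residual replication feeds the reservoir. It also gives the reference figures: a half-life of 44.2 months on HAART and 73.4 years to eradication.

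On measurement, Study development says that "the size of the reservoir of latent virus will be measured every 3 months after a blood extraction". Annex IV adds: "Two baseline determinations (three months apart) will be performed to investigate the accuracy of the method and the stability of the reservoir". The Study Plan table schedules the reservoir measurement at both baselines and at Months 3, 6, 9, 12, 15 and 18. It marks drug administration from Baseline 2 to Month 12.

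**The concern.** The hypothesis is worded in terms of reservoir size, not rate of loss. If residual replication refills the reservoir and the drug blocks that inflow, a fall to a new, lower level is as natural a prediction as steady exponential decay. This is an inference from the hypothesis and is not stated in the protocol.

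A one-off reduction and a faster continuing decay mean different things for reservoir dynamics, which the Rationale says the trial should inform. A single slope cannot separate them. Any early step followed by a plateau gives a negative slope and hence a finite half-life. That half-life would be set beside the 44.2-month reference and read as an accelerated rate. Its standard error would carry no warning, because it is computed as if the line were correct.

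**Working it through.** **The protocol's own figure.** The reservoir is put at about 10^6 cells (the superscript is lost in the text) and the half-life at 44.2 months. Time to eradication = log2(10^6) × 44.2 / 12 = 19.93 × 44.2 / 12 = 73.4 years, which matches. So the protocol itself reads a half-life as a constant rate that can be extrapolated.

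**Inputs from the protocol.** Baseline 1 is at month −3, Baseline 2 at month 0, and on-drug visits are at Months 3, 6, 9 and 12. The sample is 10 patients.

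**Assumptions not in the protocol.** The fall d on the log10 scale is complete by Month 3 and flat afterwards, with d from 0.2 to 0.5. With the same visits for every patient and no missing data, the fixed slope of the random-effects model equals the least-squares slope through the visit means.

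**Months 0 to 12, d = 0.3.** Mean time is 6.
- Sxx = 36 + 9 + 0 + 9 + 36 = 90
- Sxy = −0.3 × (−3 + 0 + 3 + 6) = −1.8
- Slope = −1.8 / 90 = −0.020 per month
- Half-life = 0.301 / 0.020 = 15.1 months

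**Other falls, same visits.**
- d = 0.2: slope −0.0133, half-life 22.6 months
- d = 0.5: slope −0.0333, half-life 9.0 months

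**Other choices of visits, d = 0.3.**
- Baseline 1 added: Sxx = 157.5, Sxy = −3.6, slope −0.0229, half-life 13.2 months
- Both baselines and Months 15 and 18 kept, with the plateau continuing: Sxx = 378, Sxy = −5.4, slope −0.0143, half-life 21.1 months

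**Step on top of the protocol's background decay.** Background slope = 0.301 / 44.2 = 0.0068 log10 per month. Adding it to the d = 0.3 step (Months 0 to 12):
- Fitted slope = −(0.020 + 0.0068) = −0.0268 per month, half-life 0.301 / 0.0268 = 11.2 months
- Five-year fall implied by that slope: 60 × 0.0268 = 1.6 log10
- Five-year fall under the scenario: 0.3 + 60 × 0.0068 = 0.71 log10
- Six-log fall: 6 / 0.0268 / 12 = about 19 years from the line, against (6 − 0.3) / 0.0068 / 12 = about 70 years under the scenario

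A slope fitted only to Months 3 to 12 excludes the step. It recovers zero in the first scenario and −0.0068 (half-life 44.2 months) in the second.

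**Precision with 10 patients.** The within-patient visit SD is not given, so I assume 0.2, 0.3 and 0.5 log10, with no variation in slope between patients.
- SE of the overall slope = SD / √(10 × 90): 0.0067, 0.010 and 0.017
- SE of the Month 3 to 12 slope = SD / √(10 × 45): 0.009, 0.014 and 0.024
- Simulated power of a 5% lack-of-fit test (visit as category against line, Months 0 to 12, 2,000 runs): for a 0.3 log10 step 65%, 31% and 13%; for a 0.5 log10 step 99%, 77% and 32%

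**The case against.** The main counter-arguments are these.

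- **A log-linear slope is a sensible primary summary.** It is parsimonious with 10 patients and directly comparable with the 44.2-month reference. This stands, and it is why the line should be kept.
- **Checks of linearity belong in an SAP, which is not shown.** A reader might infer that nothing anywhere would reveal a misfit. The protocol does not support that: an SAP or simple plots could show it. What remains is that the protocol itself fixes the linear form and the half-life derived from it.
- **The plateau is a scenario.** A reader might infer that the protocol predicts one. It does not: it expects a smaller reservoir if maintenance is dynamic and says nothing about the time course. The step sizes are assumptions too.
- **The long-term contrast can be overstated.** A reader might infer that after a one-off fall the reservoir would never reach eradication, while the line promises it. That ignores the protocol's own background decay, which leaves about 70 years against about 19. Section 11 also plans a half-life and no five-year or eradication projection.
- **Estimates come with standard errors and little weight on P values.** At an SD of 0.3, the example slope has a 95% CI of about −0.040 to 0.000; at 0.5 it is about −0.053 to +0.013. So it would not pass as firm evidence of decay. But the interval describes sampling error around a line and does not show whether the line is the right shape.
- **A linearity test would not rescue the half-life.** This is correct. At the powers above, a non-significant result would often seem to validate a misleading figure.

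**Conclusion.** The point holds as a weakness in a method that the protocol states, and it should be corrected. If the response is an early fall that levels off, the planned analysis will present it as continuing decay. The fitted half-life would be about 15 months for a 0.3 log10 fall, 13 months with Baseline 1 included, and 9 to 23 months for falls of 0.5 to 0.2 log10. With background decay continuing at 44.2 months, the slope overstates the five-year fall by about 0.9 log10 (1.6 against 0.71).

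These sizes rest on an assumed step complete by Month 3 and, for the last comparison, on extending the slope in the way the protocol's own 73.4-year figure does. The half-life also depends on which visits enter the line, which section 11 does not fix. Nothing here shows that the response will be non-linear or that the linear model must be abandoned.

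**What to change.** Keep the linear random-effects model and amend section 11 as follows.

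1. Add the same random-effects model with visit as a category: the mean of the two baselines, then Months 3, 6, 9 and 12. Report the mean change from baseline at each visit with its 95% CI.
2. Report the Month 3 to 12 slope with its 95% CI beside the overall slope.
3. Always give both with the half-life, and describe the half-life as conditional on linear decline. Do not interpret it as continuing decay unless the Month 3 to 12 slope supports that.
4. Do not make reporting depend on a lack-of-fit test.
5. State which visits enter the on-drug line, and leave out Months 15 and 18, which follow drug suspension.

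The cost is one or two extra models on measurements already scheduled, with no added blood draw or visit. The visit-specific estimates will be less precise than the line. The Month 3 to 12 slope may well be inconclusive: at an assumed SD of 0.3 its SE is 0.014, against a slope of interest of about 0.020. In that case the report should say that the data do not distinguish a one-off fall from continuing decay.

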**STUDY PLAN**

| ***Day*** | ***Baseline***  ***1*** | ***Baseline 2*** | ***Month 3*** | ***Month 6*** | ***Month 9*** | ***Month 12*** | ***Month 15*** | ***Month 18*** |
| --- | --- | --- | --- | --- | --- | --- | --- | --- |
| **Informed consent** | X |  |  |  |  |  |  |  |
| **Clinical history** | X | X | X | X | X | X | X | X |
| **Physical examination1** | X | X | X | X | X | X | X | X |
| **Pregnancy test (women)** |  | X |  |  |  |  |  |  |
| **Determination of viral tropism** | X |  |  |  |  |  |  |  |
| **Inclusion criteria** | X |  |  |  |  |  |  |  |
| **Laboratory determinations2** | X | X | X | X | X | X | X | X |
| **Administration of drugs** |  | X | X | X | X | X |  |  |
| **Evaluation of adverse effects** |  | X | X | X | X | X |  |  |

1 Includes heart rate and blood pressure.

2 Includes blood count, biochemistry, habitual immunological and virological monitoring, as well as measurement of the size of the latent reservoir, residual viremia and immune activation markers.

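### The slope and half-life come from one straight line in time, but the reservoir is measured before, during and after maraviroc and no visit window or change point is stated

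*Protocol*

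**What the plan says.** All references are to the Protocol.

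- **Model (section 11, Statistical analysis).** The frequency of infected cells is analysed by random-effects regression in which "the variable time will be introduced as an independent variable assuming linear kinetics". The time origin and response are fixed as follows: "The gradient of the log10 reduction in IUPM will be estimated according to time from the start of therapy".
- **First approach (section 11).** "2 models will be made to estimate the gradients of log10 reduction in IUPM in the group of patients treated with the drug (n=10". What separates the two models is not said. The half-life belongs to this approach: "Assuming linear reduction kinetics over time, the half-life will be calculated".
- **Second approach (section 11).** A single model that "will include an interaction term between time and the treatment received".
- **Schedule (section 7.2, Study plan).** Laboratory determinations are marked at all eight visits: Baseline 1, Baseline 2 and Months 3, 6, 9, 12, 15 and 18. The footnote to that row covers routine monitoring "as well as measurement of the size of the latent reservoir, residual viremia and immune activation markers".
- **Baselines (Annex IV, study methods).** "Two baseline determinations (three months apart) will be performed to investigate the accuracy of the method and the stability of the reservoir".
- **Treatment period.** Synopsis item 15 gives 12 months. Section 7.2 says "Treatment will be administered for at least 12 months" and places two additional visits after the drug is suspended. The Study plan marks drug administration from Baseline 2 to Month 12.
- **Design.** One arm, no control drug, no randomisation.

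**The concern.** The Protocol fixes the functional form of the primary analysis as one straight line, but its schedule has three phases: about three months before drug, twelve months on drug and six months after. Three of the eight planned assays (Baseline 1, Month 15, Month 18) carry information on off-drug change. If they enter the same line, the estimated gradient is a weighted mix of three slopes rather than the on-drug slope, and the half-life inherits the error.

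When decay is slower off drug than on drug, the mix is pulled towards no effect. An active drug could then appear to leave the reservoir's half-life close to the background value that the Protocol quotes.

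There is a related reporting problem. The half-life is the reciprocal of a slope, and section 11 reports estimates with standard errors. A symmetric standard error describes a reciprocal poorly when the slope is close to zero.

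**Working it through.** **Check of the scale.** Section 3 quotes a half-life of 44.2 months and 73.4 years to eradicate about 10^6 cells. log2(10^6) × 44.2 / 12 = 19.93 × 44.2 / 12 = 73.4 years. The Protocol's background figure is therefore log-linear decay with slope log10(2)/44.2 = 0.00681 log10 per month. Section 11 states no slope, power or SD to reproduce.

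**Inputs.** Visit times t = −3, 0, 3, 6, 9, 12, 15, 18 months (Study plan and Annex IV), with drug from 0 to 12. With balanced, complete data the fixed slope of a linear random-effects model equals the least-squares slope. The off-drug course is not given, so it is varied.

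**Pooled slope.** Mean t = 7.5 and Sxx = 2 × (10.5² + 7.5² + 4.5² + 1.5²) = 378. For a path with slope p before, b during and q after drug:

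- before: (−10.5)(−3) = 31.5, weight 31.5/378 = 0.083
- during: −4.5×3 − 1.5×6 + 1.5×9 + 4.5×12 + 7.5×12 + 10.5×12 = 261, weight 261/378 = 0.690
- after: 7.5×3 + 10.5×6 = 85.5, weight 85.5/378 = 0.226

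Fitted slope = 0.083p + 0.690b + 0.226q. The weights sum to 1, so there is no dilution if p = q = b.

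| Assumed off-drug course | Fitted / true on-drug slope | True half-life of 12 months is reported as |
|---|---|---|
| Flat before, decline continues after | 0.690 + 0.226 = 0.92 | 13.1 |
| 44.2-month background decay before and after | 0.690 + 0.310 × 12/44.2 = 0.77 | 15.5 |
| Flat before and after | 0.69 | 17.4 |
| Flat before, linear return to baseline by Month 18 (q = −2b) | 90/378 = 0.24 | 50.4 |
| Flat before, back at baseline by Month 15 | 45/378 = 0.12 | 100.8 |

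Under background decay the ratio is 0.73 for a true on-drug half-life of 6 months and 0.85 for 22.1 months.

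**Narrower windows.**

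- Visits 0 to 18: Sxx = 252. The ratio is 180/252 = 0.71 (flat after) or 36/252 = 0.14 (return by Month 18). Dropping Baseline 1 alone does not remove the problem.
- Visits −3 to 12, flat before drug: 0.86.
- Visits 0 to 12, or a piecewise line with knots at 0 and 12: 1.00 under the flat course and under linear return by Month 18.

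**The time-by-treatment interaction.** With treatment coded 1 at Months 3 to 12 and 0 otherwise, and its main effect included, the on-drug slope is recovered (1.00). Without the main effect the ratio is 0.90 (flat off drug) or 0.96 (return by Month 18).

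**Precision.** Assume a within-patient residual SD of 0.3 log10 and 10 complete patients, and leave aside between-patient variation in slope.

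- One line, eight visits: 0.3/√(10 × 378) = 0.0049 log10/month
- Months 0 to 12, five visits (Sxx = 90): 0.3/√(10 × 90) = 0.0100
- Piecewise, eight visits: 0.102 × 0.3/√10 = 0.0096

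**Half-life standard error.** At the 44.2-month rate, the delta-method SE is 0.301/0.00681² × SE(slope). That is about 32 months with the eight-visit SE and about 65 months with the five-visit SE. Inverting the slope's 95% limits gives:

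- eight visits: 0.00681 ± 1.96 × 0.0049 = −0.0028 to 0.0164, so a half-life from 0.301/0.0164 = 18 months to no decay
- five visits: −0.0128 to 0.0264, so from 11 months to no decay

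**The case against.** A reader might infer that the Protocol commits to one line through all eight visits and that the drug effect is therefore strongly diluted by design. The documents do not support that.

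- **Pooling is not stated.** It is the plain reading of a linear time term with no restriction, but no passage says that every visit enters. Some text leans towards an on-drug window: time runs from the start of therapy, follow-up is given as 12 months (Synopsis item 16, section 4.5), the post-drug visits are called additional, and Annex IV gives the paired baselines a purpose of their own.
- **The two models and the interaction might separate the periods.** In a single-arm trial the interaction is estimable only if treatment is coded on and off over time, and such coding can recover the on-drug slope.
- **Severe dilution needs a rebound.** Ratios of 0.24 and 0.12 require a full return to baseline within three to six months of stopping. No passage predicts that or says that the late visits are there to detect it.
- **The half-life SE of 65 months belongs to the five-visit analysis.** For the pooled line it is about 32 months. It is finite. The fault is the symmetric interval.

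These points limit the size and certainty of the concern without removing it. The half-life sits in the first approach, which has no interaction. Nothing says that its two models divide on-drug from off-drug time, and the required coding of treatment is not stated. Counting time from the start of therapy still leaves Months 15 and 18 in. Visit selection may be left to a statistical analysis plan, but the Protocol itself fixes a straight line that does not fit its own schedule.

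**Conclusion.** The concern holds as a should-fix. Section 11 specifies a linear time term and a half-life derived from it without saying which visits enter or allowing a change at drug start or stop.

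If all scheduled visits enter one line, the on-drug slope is understated by about 8% when the decline continues after stopping, and by 15 to 31% under background decay or a plateau off drug. The understatement reaches 76 to 88% only under a full return to baseline. These figures assume complete data, linear segments and the stated off-drug courses, none of which the Protocol gives. The direction depends on decay being slower off drug than on drug; if the rates are equal there is no bias.

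The severity stops at should-fix because the trial is an exploratory pilot that puts no emphasis on P values, and because pooling is inferred rather than stated.

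**What to change.** In section 11:

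1. Make the on-drug slope of log10 IUPM the primary estimate. Either fit a piecewise-linear random-effects model with knots at each patient's actual first and last maraviroc dose, or use only the visits from Baseline 2 to the last dose. In the piecewise model Baseline 1 informs the pre-drug segment and Months 15 and 18 the post-drug segment. Coding both baselines as time 0 is acceptable only if a flat pre-drug trend is assumed, and that assumption should be written down.
2. Say what the two models of the first approach are. If the second approach stays, define the treatment term as a time-varying on/off indicator and include its main effect.
3. Compute the half-life from the on-drug slope only. Obtain its interval by inverting the slope's confidence limits, with no decay reported where a limit crosses zero, in place of a symmetric standard error.

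Reconcile Synopsis item 15, section 7.2 and the Month 12 drug-administration entry in the Study plan on how long treatment lasts, because the boundary between on-drug and off-drug time depends on it.

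The change is to wording and uses assays already planned. The cost is precision: the slope's SE rises from about 0.005 to about 0.010 log10 per month at the assumed SD of 0.3.
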